#### Economic assessment

One aim of the feasibility trial is to develop a framework to perform a cost-effectiveness evaluation of the intervention if a full trial evaluation is conducted in the future. As such, the feasibility trial will focus on identifying all of the inputs that would be necessary for such an evaluation at four stages. This approach to deriving costing follows the methods applied in recent research in a school setting [34]. Resources used at stage one (project development), stage two (planning), stage three (delivery) and stage four (present the Action 3:30 programme) will be identified separately. By collecting this cost information we will be able to assess the feasibility, appropriateness, advantages and disadvantages of the data collection methods and tools that would be needed for the economic evaluation of a trial. Timesheet and expense data will be collected for all resources used to deliver the Action 3:30 intervention at each stage of planning and delivery, from a public sector perspective.

#### Post-study qualitative work

Qualitative research will be conducted with intervention participants, TAs and school administrators at the end of the intervention to inform any necessary revisions to elements of the intervention training and delivery. The qualitative work that will be conducted with each group is summarized next.

##### Intervention participants (children)

A focus group will be conducted –in each intervention school. The groups will include high-attending pupils (pupils in the middle and highest thirds of attendance) and low-attending pupils (pupils in the lowest third of attendance). We aim to achieve a balance of boys and girls in each group. The focus groups will examine aspects of the programme that the children enjoyed, elements they did not enjoy, factors that either positively or negatively affected recruitment and any suggestions on how to improve the intervention.

##### Teaching assistants

Intervention school TAs will be asked to take part in a semi-structured interview focusing on their experiences of the Action 3:30 project, including their opinions of the training and intervention resources, session delivery, areas of success and challenge, and recommendations for refinement of the intervention. The TAs will also be asked to comment qualitatively on how the training programme affected their perceived ability to lead PA sessions and their thoughts on what would need to be done to maintain this provision once the intervention ends.

##### School administrators

We will interview the member of staff at five intervention and five control schools (not the TAs) who was the main project liaison or administrator contact. The schools will be purposefully selected based on the implementation rates (high or low) of the project. The role of this person will vary between schools but it is likely that she or he will be either head or deputy head teacher, a head of Year 5 or 6 or the person responsible for health and well-being in the school. The interviews will examine perspectives on the operation of the Action 3:30 trial in their school, including the perceived value of training TAs, why the school signed up to the trial, aspects that did and did not work, and suggested refinements to the intervention. Intervention school administrators will also be asked to comment on what resources, training and funding would be necessary to continue the provision of the activity sessions once the trial funding has ended.

### Sample size

The target sample size is 30 Year 5 and 6 children per school, thus yielding 300 intervention and 300 control participants. The feasibility trial is being conducted to provide the information necessary to conduct an adequately powered cluster randomized controlled trial (cluster RCT). Previous research suggests that a cluster RCT that is designed to detect change in accelerometer-determined PA levels could involve between 40 and 80 schools [35,36]. Thus, to estimate the sample size for such a trial there is a need to determine variability in PA and intraclass correlation coefficient. Although we have not conducted a conventional sample size estimate for between-group comparisons, 600 participants will provide a margin of error of ±6% for adherence to intervention and ±4% for collection of outcome data.

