**Methods/Design:**

A feasibility trial will be conducted in 20 primary schools. Schools will be randomly assigned to intervention or control arms. Intervention schools will receive a 25-hour TA training programme for two TAs, a first-aid certificate course for two TAs; ongoing TA support; 40 one-hour session plans that can be delivered by TAs; Action 3:30 clubs that run twice a week for 20 weeks; and ten sets of parent information sheets that are distributed biweekly.

All measures will be assessed at baseline (Time 0), at the end of the intervention period (Time 1) and four months after the intervention has ended (Time 2). As this is a feasibility study, our primary interest is in estimating the recruitment of schools and children, adherence to the intervention, and completeness of data collection for outcomes and costs.

As the most likely primary outcome measure in a future definitive trial will be accelerometer-determined minutes of moderate-to-vigorous PA (MVPA) per day, participants will wear accelerometers for five days (including two weekend days). Several psychosocial variables that could act as mediators in a future trial will be assessed via a questionnaire. Process evaluations of the session attendance, perceived enjoyment and perceived exertion will be assessed during the intervention. At the end of the intervention period, qualitative assessments will be conducted to identify how the programme could be improved before proceeding to a larger trial.

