## Methods/Design

Action 3:30 is an after-school PA programme that is taught by TAs within the school (see intervention details). The feasibility trial will be conducted in 20 primary schools recruited from the Greater Bristol area. Randomization will take place once all schools have been recruited and after baseline data collection. Balance between trial arms will be achieved with respect to local education authority membership, deprivation, ratio of Year 5 to Year 6 pupils, proportion of female participants, and mean minutes of moderate-to-vigorous PA (MVPA) at baseline. This will be achieved by calculating an imbalance statistic [17] for all possible allocation sequences with at least two intervention schools per local education authority, then randomly selecting one sequence from a subset with the most desirable balance properties. This process will be performed by an independent statistician.

We aim to recruit 30 Year 5 or 6 pupils from each primary school. Previous research indicates that a majority of children are not currently meeting PA recommendations [3,4] and almost all children would benefit from an increase in PA. The programme will be oriented to general physical skills development and activity rather than specific sports skills, with the hope of attracting children not already involved in team sports. Therefore, all Year 5 and 6 children who are physically able to engage in PE classes will be eligible to participate in the sessions. In schools where more than 30 children consent, and are eligible to participate, 30 will be randomly selected for the study by the research team.

The project was approved by the ethics and research committee of the School for Policy Studies at the University of Bristol. Written informed parental consent was obtained for all participants.

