#### Action 3:30 clubs

Action 3:30 clubs will be instigated in each of the ten intervention schools. The clubs will run for one hour after school, twice per week, for 20 weeks. During the clubs, the two TAs that have attended the training programme will deliver the session plans.

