### Data and economic analyses

#### Quantitative analyses

As a feasibility trial, the main analyses will focus on data relating to recruitment, intervention adherence and feasibility of data collection, and will mainly be descriptive in nature (means (with standard deviation) or *N* (number, as a percentage), as appropriate). School associated intraclass correlation coefficient s will be estimated for possible primary outcomes for a future trial. Mean session attendance will be calculated. The loss to follow-up rate for both groups will be identified. We will estimate between-group differences in MVPA using appropriate multi-level regression models, but the focus will be on the inclusion or exclusion of meaningful effects within the 95% confidence intervals. *P* values will not be considered.

The economic analyses will estimate the direct and indirect resource use collected in line with the direct cost items listed in recent NICE guidance [37] and associated costs of programme delivery for the students themselves and their parents and carers. A framework for an appropriate, relevant and feasible trial economic evaluation will be developed.

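### The only stated precision (±6% adherence, ±4% outcome data) matches margins for independent children and makes no stated allowance for school clustering

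*Protocol article*

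**What the plan says.** The abstract of the protocol article sets out a school-randomised design: "A feasibility trial will be conducted in 20 primary schools", and "Schools will be randomly assigned to intervention or control arms". The Sample size section adds: "The target sample size is 30 Year 5 and 6 children per school, thus yielding 300 intervention and 300 control participants". Under Action 3:30 clubs the article says that "Action 3:30 clubs will be instigated in each of the ten intervention schools", and the Process evaluation section has attendance recorded by the teaching assistants in those ten schools only.

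The Sample size section states that no conventional calculation was made for between-group comparisons. It then offers one precision statement in its place: "600 participants will provide a margin of error of ±6% for adherence to intervention and ±4% for collection of outcome data". It gives no confidence level, assumed proportion, ICC or design effect for these margins.

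Clustering is recognised elsewhere. The Sample size section says that the ICC is needed to plan the definitive trial. The Quantitative analyses section says: "School associated intraclass correlation coefficient s will be estimated for possible primary outcomes for a future trial". That section also plans multi-level models for the MVPA comparison.

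**The concern.** The abstract and the Measures section name recruitment, adherence and completeness of data as the study's primary interest. The two margins are the only numerical statement of how well any of these will be estimated, and they are the only quantitative support given for 600 children.

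Children in one school share the same two teaching assistants, the same club and the same data collection visits, so some similarity within schools in attendance and data return is plausible. The School administrators section plans to choose interviewees' schools by high or low implementation, so the authors allow for differences between schools. If such similarity exists, 300 or 600 children carry less information than the same number of independent children. A team planning the definitive trial could then take the adherence and completion estimates as firmer than they are.

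**Working it through.** **Inputs from the article**
- Children per school: m = 30 (Sample size).
- Adherence: 10 intervention schools, n = 300.
- Outcome data: 20 schools, n = 600, since loss to follow-up is to be reported for both arms (Quantitative analyses).

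**Assumptions, because the article gives no value**
- Confidence level: 95% two-sided, the level used for intervals in Quantitative analyses.
- Proportion p: 0.5 as the worst case, with 0.8 and 0.9 as alternatives.
- ICC: 0.02, 0.05 and 0.10.

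**Step 1. Reproduce the stated figures.** Half-width = 1.96 × √(p(1−p)/n).
- Adherence: 1.96 × √(0.25/300) = 5.66%, which rounds to ±6%.
- Outcome data: 1.96 × √(0.25/600) = 4.00%, which is ±4%.

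With 600 independent children no proportion gives ±6% at 95%, because the maximum is 4.00%. The 90% and 99% levels give at most 3.36% and 5.26%. So the adherence figure was evidently calculated on 300 children.

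**Step 2. Add the design effect.** DE = 1 + (m − 1) × ICC = 1 + 29 × ICC. Half-width = 1.96 × √(p(1−p) × DE/n). At p = 0.5:

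| Assumed ICC | DE | Adherence (300 in 10 schools) | Outcome data (600 in 20 schools) |
|---|---|---|---|
| 0 | 1.00 | ±5.7% | ±4.0% |
| 0.02 | 1.58 | ±7.1% | ±5.0% |
| 0.05 | 2.45 | ±8.9% | ±6.3% |
| 0.10 | 3.90 | ±11.2% | ±7.9% |

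At ICC 0.05 the effective sample sizes are 300/2.45 ≈ 122 and 600/2.45 ≈ 245. Replacing 1.96 by the t value on 9 and 19 degrees of freedom widens the ICC 0.05 margins to about ±10.2% and ±6.7%.

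**Step 3. Vary the proportion.**
- p = 0.8, ICC 0.05: 1.96 × √(0.16 × 2.45/300) = 7.1%; with 600, 5.0%.
- p = 0.9, ICC 0.05: 1.96 × √(0.09 × 2.45/300) = 5.3%; with 600, 3.8%. Both lie inside the stated margins.
- p = 0.9, ICC 0.10: 1.96 × √(0.09 × 3.90/300) = 6.7%; with 600, 4.7%.

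**Step 4. Find the largest ICC at which the stated margins still hold.** Setting the half-width equal to the stated margin M gives ICC = [(M / unclustered half-width)² − 1]/29.

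| p | Adherence, ±6% | Outcome data, ±4% |
|---|---|---|
| 0.5 | 0.004 | 0 |
| 0.8 | 0.026 | 0.019 |
| 0.9 | 0.073 | 0.061 |

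**The case against.** The strongest reply is that p = 0.5 is a conservative choice and leaves room for some clustering. This partly stands. If adherence and completion are near 0.9, the stated margins survive an ICC of 0.05. The half-width depends only on the product p(1−p) × DE, so p = 0.8 with ICC 0.02 also gives about 5.7% and 4.0%, which round to the printed figures. But the article states neither a proportion nor an ICC, so a reader cannot tell that any such allowance was intended, and at p = 0.8 the room is used up by an ICC of about 0.02 to 0.03.

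A second reply is that this is a feasibility study with no hypothesis test and no progression threshold tied to either margin. That is true and limits the consequence. It does not make the stated figures right for a clustered sample.

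Four stronger readings are tempting, and the article does not support them.
- A reader might infer that crediting 600 children to adherence has narrowed that margin. It has not: ±6% is already the figure for 300, and the same section gives the split ("thus yielding 300 intervention and 300 control participants"). Only the attribution in the sentence is loose.
- A reader might treat 600 as an unacknowledged ceiling, because in schools with more than 30 eligible, consenting children "30 will be randomly selected for the study by the research team". But 30 per school is described as a target, and computing a planning margin at the target is normal.
- A reader might assert that attendance and data return depend strongly on the school. Some dependence is plausible, but the article gives no figure for it.
- A reader might conclude that the final percentages will be reported without clustered intervals. The article calls the analyses mainly descriptive and does not rule such intervals out. That detail is commonly left to a fuller document.

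**Conclusion.** The point holds as an omitted design effect in the study's only precision statement. At p = 0.5, the proportion at which the figures reproduce without clustering, the stated ±4% is exceeded for any positive ICC and the stated ±6% once the ICC passes about 0.004. For ICCs of 0.02 to 0.10 the shortfall at p = 0.5 is roughly 1 to 5 percentage points for adherence (7.1 − 6 = 1.1; 11.2 − 6 = 5.2) and 1 to 4 for outcome data (5.0 − 4 = 1.0; 7.9 − 4 = 3.9).

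It would go too far to say flatly that both margins are too narrow. That depends on an ICC and a proportion that the article does not give, and the stated margins remain adequate if the ICC is near zero or the proportion is extreme. The sizes above also assume equal schools of 30 and use the normal multiplier; t multipliers for 10 or 20 schools would widen them further.

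**What to change.** Restate the precision sentence in the Sample size section with a design effect, and give the assumed ICC range, proportion and confidence level. Name the base for each margin: 300 children in 10 schools for adherence, 600 children in 20 schools for outcome data. Naming the base corrects the wording and does not itself change the ±6%.

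Possible wording, with the ICCs marked as assumptions: *With 10 intervention schools of 30 children, the 95% margin for an adherence proportion of 0.5 is about ±9% at an ICC of 0.05 and ±11% at 0.10. With 20 schools of 30, the margin for outcome completion is about ±6% and ±8%. The margins are smaller if the proportions are further from 0.5.* If t multipliers are preferred because there are few schools, say so and use them throughout.

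Any confidence interval later reported for these percentages should allow for school clustering.

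The cost is one rewritten sentence and less favourable stated margins. The design and the recruitment target do not change.

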### Data and economic analyses

#### Quantitative analyses

As a feasibility trial, the main analyses will focus on data relating to recruitment, intervention adherence and feasibility of data collection, and will mainly be descriptive in nature (means (with standard deviation) or *N* (number, as a percentage), as appropriate). School associated intraclass correlation coefficient s will be estimated for possible primary outcomes for a future trial. Mean session attendance will be calculated. The loss to follow-up rate for both groups will be identified. We will estimate between-group differences in MVPA using appropriate multi-level regression models, but the focus will be on the inclusion or exclusion of meaningful effects within the 95% confidence intervals. *P* values will not be considered.

The economic analyses will estimate the direct and indirect resource use collected in line with the direct cost items listed in recent NICE guidance [37] and associated costs of programme delivery for the students themselves and their parents and carers. A framework for an appropriate, relevant and feasible trial economic evaluation will be developed.

#### Qualitative analysis

All focus group and interview recordings will be transcribed verbatim and anonymized. As the data are exploratory, we will adopt a thematic analytical approach. Meaningful content will be coded and codes grouped to form themes that describe the content of codes [38]. Quotations deemed to best represent the nature of each theme will then be extracted. This process will be conducted independently for the pupil focus groups, TAs and school administrators. Data from the three sources will then be compared to establish if there are any consistencies and discrepancies in the reports from the three groups.

## Discussion

This paper describes the protocol for the Action 3:30 feasibility trial, which is attempting to increase PA among Year 5 and 6 children attending UK primary schools. Many children do not engage in sufficient amounts of PA. Primary school is a key period for the establishment of PA behaviours, preferences and skills. The after-school period is well-established for the delivery of extracurricular programmes but there is an absence of well-researched, well-evaluated after-school interventions. Action 3:30 is a new intervention that is designed to train TAs to deliver PA programmes in UK primary schools. The goal of the feasibility trial is to assess the potential of this innovative intervention approach and provide all the information necessary to design a cluster RCT.

## Trial Status

Intervention on-going with contact sessions due to end July 2013 and data collection due to be completed by December 2013.

### Current study status (11/09/2012)

We have obtained ethical approval and funding for the Action 3:30 study and have recruited all project staff. Invitations to participate in the study were sent to 132 schools (31, Bristol City Council; 51, Bath and North East Somerset Council; 50 South Gloucestershire Council) within a 20-mile radius of the university department that was not participating in current university evaluations of school-based PA interventions. Twenty schools consented to participate (a further three were added to a reserve list), two expressed an interest but did not enrol due to a shortage of Year 5 and 6 pupils and a shortage of space. One hundred and seven schools did not reply. Participant recruitment began in all 20 schools in September 2012 with baseline data collection due to be completed by late October 2012. TA training will commence in mid-November 2012.

## Abbreviations

CDO: Coach Development Officer; CSLA: Community Sports Leader Award; MVPA: moderate-to-vigorous intensity physical activity; NICE: National Institute for Health and Clinical Excellence; PA: physical activity; PE: physical education; RCT: randomized controlled trial; TA: teaching assistant.
